## Abstract

**Background:**

Acute lung injury complicates approximately 25-30% of subjects undergoing oesophagectomy. Experimental studies suggest that treatment with beta agonists may prevent the development of acute lung injury by decreasing inflammatory cell infiltration, activation and inflammatory cytokine release, enhancing basal alveolar fluid clearance and improving alveolar capillary barrier function.

**Methods/Design:**

The Beta Agonist Lung Injury TrIal (prevention) is a multi-centre, randomised, double blind, placebo-controlled trial. The aim of the trial is to determine in patients undergoing elective transthoracic oesphagectomy, if treatment with inhaled salmeterol 100 mcg twice daily started at induction of anaesthesia and continued for 72 hours thereafter compared to placebo affect the incidence of early acute lung injury and other clinical, resource and patient focused outcomes. The primary outcome will be the development of acute lung injury within 72 hours of oesophagectomy. The trial secondary outcomes are the development of acute lung injury during the first 28 days post operatively; PaO_2_: FiO_2 _ratio; the number of ventilator and organ failure free days, 28 and 90 day survival; health related quality of life and resource utilisation. The study aims to recruit 360 patients from 10 UK centres.

**Trial registration number:**

Current Controlled Trials ISRCTN47481946

## Background

Acute Lung Injury (ALI) and the Acute Respiratory Distress Syndrome (ARDS) occur in response to a wide variety of insults including traumatic injuries, sepsis, multiple blood transfusions, pneumonia or aspiration of gastric contents. The syndrome carries with it significant morbidity[1], a significant risk of death[2], prolonged hospital stay and high treatment costs[3]. The pathophysiological changes seen in ALI/ARDS comprise systemic and alveolar inflammation, increased pulmonary vascular permeability and alveolar capillary damage[4]. This causes flooding of the alveolar space which reduces pulmonary compliance, interferes with ventilation perfusion matching and results in hypoxaemia, and acute respiratory failure.

ALI/ARDS complicates approximately 25-30% of subjects undergoing oesophagectomy[5-8]. One lung ventilation which is used during the transthoracic approach to oesophagectomy is implicated in the pathogenesis of ALI/ARDS[4,9]. It invokes an ischaemia-reperfusion injury on the deflated lung, whilst the ventilated lung is exposed to oxygen toxicity and high inflation pressures which cause ventilator associated lung injury. Thus patients undergoing oesophagectomy with one lung ventilation are at high risk of developing ALI/ARDS and may serve as a group of people in whom prophylactic strategies to prevent the development of lung injury may be considered[10].

### Rationale for beta agonists in the prevention of ALI/ARDS

#### Inflammation

β_2 _agonists reduce neutrophil sequestration, activation and inflammatory cytokine production *in-vitro *and in animal models of ARDS[11]. In humans, inhaled salmeterol (long acting β_2 _agonist) given prior to lipopolysaccharide inhalation reduces neutrophil influx, degranulation and tumour necrosis factor α release[12]. However in the single centre randomised controlled trial (BALTI-1), although salbutamol increased circulating neutrophil numbers, it had no effect on alveolar neutrophil sequestration, activation or alveolar cytokine levels[13]. A potential explanation for this finding is that the administration of a β_2 _agonist after the clinical manifestations of ARDS are apparent may be too late to prevent the early inflammatory influx.

#### Endothelial / epithelial function

The balance between oedema formation and clearance is influenced by the degree of alveolar-capillary permeability, pulmonary capillary hydrostatic and oncotic pressures, and rate of active alveolar fluid clearance[14]. β_2 _agonists may reduce oedema formation through enhancing alveolar-capillary barrier function. Animal and human studies [15,16] report improvement in endothelial barrier function as well as providing epithelial cytoprotection against infection[11]. In BALTI-1, there was *in-vivo *evidence of reduced alveolar capillary permeability and *in-vitro *evidence of enhanced epithelial monolayer wound repair in subjects treated with salbutamol[17].

Experimental studies in animals, and *ex-vivo *human lung show that both intravenous and inhaled β adrenergic agonists accelerate the rate of alveolar fluid clearance thus hastening resolution of non-cardiogenic pulmonary oedema[18]. Evidence of their potential efficacy in humans was first shown by Sartori *et al *who used inhaled salmeterol to prevent the development of high altitude pulmonary oedema in mountaineers[19]. In patients with ARDS, the phase II randomised controlled trial BALTI-1 found that intravenous salbutamol significantly reduced lung water and improved lung mechanics ARDS[20].

In summary, the potential of prophylactic administration of β_2 _agonists in subjects at high risk of developing ARDS has not previously been evaluated. Theoretically the administration of treatment prior to injury has the potential to reduce the development of lung injury through decreasing inflammatory cell infiltration, activation and inflammatory cytokine release, enhancing basal alveolar fluid clearance and improving alveolar capillary barrier function. This study aims to define the effectiveness of inhaled salmeterol (a long acting β_2 _agonist) for the prevention of ALI/ARDS in a group of subjects at high risk of developing the condition. The treatment is simple and known to be well tolerated in people with obstructive lung diseases and if effective could be easily incorporated into widespread clinical practice. The results from this trial will provide the basis for future clinical studies investigating this and other preventative strategies in broader subject groups known to be at risk of ARDS (such as pneumonia and sepsis).

The Beta Agonist Lung Injury TrIal (prevention) [BALTI-prevention] is a multi-centre, randomised, double blind, placebo-controlled trial. The aim of the trial is to determine in patients undergoing elective transthoracic oesphagectomy, if treatment with inhaled salmeterol 10 0mcg twice daily started at induction of anaesthesia and continued for 72 hours thereafter compared to placebo affect the incidence of early acute lung injury and other clinical, resource and patient focused outcomes.

## Methods / Design

### Trial Approvals and Conduct

The trial is approved by South Birmingham Research Ethics committee. The trial is registered on the International Standard Randomised Controlled Trial Registry (ISRCTN47481946). The sponsor organisation for the trial is Heart of England NHS Foundation Trust. The trial is being coordinated by the Warwick Clinical Trials Unit (http://www.warwick.ac.uk/go/ctu). The trial is funded by the National Institute for Health Research (NIHR) Research for Patient Benefit Programme (PB-PG-0408-16104). Further details can be found on the trial website (http://www2.warwick.ac.uk/fac/med/research/ctu/trials/ecr/baltiprevention). The trial will be carried out in accordance with the Medical Research Council (MRC) Good Clinical Practice Guidelines, applicable UK legislation and the Standard Operating Procedures of the Warwick Clinical Trials Unit. The trial will be reported in line with the Consolidated Standards of Reporting Trials (CONSORT) 2010 guidelines[21].

### Outcome measures

#### Primary outcome

The primary outcome will be the development of acute lung injury within 72 hours of oesophagectomy. Lung injury will be defined by the American European Consensus conference definition[22] as the acute onset of (1) Bilateral infiltrates on the chest xray (2) Hypoxaemia with a PaO_2 _: FiO_2 _ratio of < 40 kPa (3) absence of clinical evidence of left atrial hypertension. The presence of absence of ALI will be determined by a trial end-point committee who will review chest xrays and physiological data from trial participants. The time window of 72 hours has been selected to exclude ALI/ARDS which may occur as a consequence of surgical complications e.g. anastamotic leak, ventilator associated pneumonia which occur later in the post-operative course.

#### Secondary outcomes

The trial secondary outcomes are the development of ALI/ARDS during the first 28 days post operatively; PaO_2 _: FiO_2 _ratio; the number of ventilator and organ failure free days, 28 and 90 day survival; health related quality of life and resource utilisation.

Ventilator free days are defined in accordance with the ARDSnet criteria[23] as the number of calendar days after initiating unassisted breathing to day 28 after randomisation, assuming a patient survives for at least 48 consecutive hours after initiating unassisted breathing. Un-assisted breathing is defined as one of at least 48 consecutive hours of (1) being extubated with face mask, nasal prong oxygen, or room air (2) T-tube breathing (3)Tracheostomy mask breathing, CPAP = 5 cm H_2_0 without pressure support of intermittent mandatory ventilation assistance. For example, if a subject initiates unassisted breathing on day 16 and survives to day 28, he/she will be assigned a value of 12 VFDs. If a similar subject begins unassisted breathing on day 16 but dies on day 25, the VFDs is 9. If a subject survives for >48 consecutive hours of unassisted breathing but requires assisted breathing (for any reason) before day 28, he/she will be assigned only the number of days of unassisted breathing before day 28. Subjects who die without initiating unassisted breathing or before 48 consecutive hours of unassisted breathing will be assigned a value of zero VFDs. Subjects transferred to another hospital or other health care facility prior to day 28 (intermediate care, nursing home etc.) while still on positive pressure ventilation will be followed up to assess this efficacy measure.

Organ failure free days are defined in a similar manner to ventilator free days with an organ failure free day being a day without evidence of non-respiratory organ failure. Organ failure will be defined as a sequential organ failure assessment (SOFA) score of greater than 3[24].

Health related quality of life will be measured using EuroQol (EQ-5D). Data will be collected at baseline, 28 days and 90 days. Resource utilisation (intensive care and hospital length of stay) will be recording. The cost of intervention and resource use will be compared.

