#### Drug administration

Subjects will receive either 100 mcg inhaled salmeterol or placebo via a spacer device within two hours of induction of anaesthesia and then 12 hourly for 72 hours. The drug will be administered by qualified medical or nursing staff. Whenever possible, subjects will be extubated at the end of surgery. Subjects requiring ventilation post operatively will receive 100 mcg of the drug via an in-line chamber inserted into the inspiratory limb of the ventilator circuit.

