### Statistical analysis plan

The primary analysis will be based on 'Intention-to-treat' (ITT). In the ITT analyses, patients will be analysed according to the treatment they were randomised to, irrespective of the treatment they actually received. In addition a per-protocol analysis will be conducted. Patients that did not proceed with planned surgery or did not receive the pre-operative dose of drug will be excluded.

Multiple imputation methods will be used to impute missing data. Prior to an imputation, the data mechanisms (MAR - missing at random; NMAR - not missing at random; MCAR - missing completely at random) will be assessed to make sure that multiple imputation is viable. Only data that is validly missing will be imputed. In the case of multivariate normal data, the multiple imputation methods assuming normality will be used. In the case where one cannot assume a distribution of the data, the ICE (imputation by chain equations) will be used. The imputed (intention to treat and adherence to protocol) datasets will be used for sensitivity analyses.

The primary outcome measure will be compared between treatment groups using a logistic regression model, with the dependent variable as acute lung injury/no acute lung injury within 72 hours and the independent variables as treatment and other important predictors (e.g. centre and age). An odds ratio measuring the treatment effect and its 95% confidence interval will be reported.

Categorical data will be analysed using logistic regression models, with treatment group as an independent variable along with other important predictors. The summary statistics will be based on proportions and the 95% CI. Continuous data: Continuous data will be analysed using linear regression models, with treatment group as an independent variable along with other important predictors. Difference in treatment will be based on adjusted mean estimates and 95% CI's. Time to event data will be analysed using a log-rank test. Any patients who have not experienced an event at the time point of interest or withdrawn will be censored. The proportion experiencing an event over time will be illustrated using a Kaplan-Meier curve for each of the treatment groups. The p-values and a hazard ratio with its 95% CI from a Cox proportional hazards model will also be presented. The proportional hazard assumption across treatment arms will be checked graphically using a log-cumulative hazard plot.

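### Ventilator free days and organ failure free days keep the days earned before death, so a patient who dies can outscore a survivor

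*Protocol article*

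**What the plan says.** Under Secondary outcomes, the protocol article counts VFDs from the start of unassisted breathing to day 28 after randomisation, "assuming a patient survives for at least 48 consecutive hours after initiating unassisted breathing". Two worked examples follow. For the survivor, "if a subject initiates unassisted breathing on day 16 and survives to day 28, he/she will be assigned a value of 12 VFDs". For the death, "If a similar subject begins unassisted breathing on day 16 but dies on day 25, the VFDs is 9".

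The only deaths scored zero are the early ones: "Subjects who die without initiating unassisted breathing or before 48 consecutive hours of unassisted breathing will be assigned a value of zero VFDs". A patient who has passed 48 hours and then needs assisted breathing again is credited only with the unassisted days.

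Organ failure free days have no worked example of their own: "Organ failure free days are defined in a similar manner to ventilator free days". Survival at 28 and 90 days is listed separately among the secondary outcomes.

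Under Drug administration: "Whenever possible, subjects will be extubated at the end of surgery".

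**The concern.** A day-count outcome of this kind is read as higher is better. That reading fails if death merely stops the count. In a population that mostly breathes unassisted from the day of surgery, a patient who dies in week three or four has already earned most of the available days, while a survivor with a long ventilator course has not.

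Late deaths are foreseeable here. The Primary outcome section itself says that anastomotic leak and ventilator-associated pneumonia arise later in the post-operative course.

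At stake is the direction of a treatment comparison on two secondary outcomes. An arm with more deaths could appear no worse, or better, on both.

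**Working it through.** **Inputs.** S is the day unassisted breathing starts, D is the day of death, and the horizon is day 28 (Secondary outcomes). An early S for most patients follows from the extubation statement under Drug administration. The particular values S = 0 or 1 are my illustration of it.

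**Rule as written, without re-ventilation.** For a survivor, VFD = 28 − S. For a death at least 48 hours after S, VFD = min(28, D) − S. For any other death, VFD = 0.

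**The article's own figures.** Survivor: 28 − 16 = 12. Death: 25 − 16 = 9. Both reproduce. In this pair the death keeps 9/12 = 75% of the credit and ranks below its matching survivor, so the example alone does not show an inversion.

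**Early start, later death.** A death scoring v outranks every survivor whose S is later than 28 − v.

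| S | D | VFD | Outranks survivors starting after day |
|---|---|---|---|
| 1 | 25 | 24 | 4 |
| 1 | 20 | 19 | 9 |
| 1 | 14 | 13 | 15 |

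All three deaths score above the article's day-16 survivor (12). The first keeps 24 of a possible 27, or 89%.

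**With re-ventilation before death.** Extubated on day 0, re-ventilated on day 10, dead on day 20: 10 VFDs. A survivor ventilated to day 20 scores 28 − 20 = 8. The deduction reduces the credit, and this death now falls below the day-16 survivor, but inversion against other survivors remains.

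**Arm level (illustration).** Take ten patients per arm, nine of them surviving with S = 1 (27 each). If the tenth in arm A starts on day 1 and dies on day 25, the mean is (9 × 27 + 24)/10 = 26.7. If the tenth in arm B survives but starts on day 5, the mean is (9 × 27 + 23)/10 = 26.6. The arm with the death scores higher.

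**Organ failure free days.** The same arithmetic carries over by the stated analogy: days without organ failure before death are kept.

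**After scoring any death by day 28 as 0.** The example death moves from 9 to 0. Survivors score 28 − S, which is at least 0, so no death can outrank a survivor. A tie at 0 is possible with a survivor who never breathes unassisted by day 28.

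**Effect on power (simulated, 168 per arm, assumed distributions).**
- Mortality-only difference, assumed 10% v 4%: power of a comparison of means rises from 27–38% to about 56%. For a rank comparison it moves from 18–21% to 23–24%.
- Effect acting only through acute lung injury (25% v 12.5%, assumed mortality of 10–30% and ventilation in 30–80% of such cases): power of a comparison of means is 18–47% with the current score and 16–38% with zero for death.

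The article gives no mortality, ventilation times or standard deviations, so these figures show only that the change can help or cost power.

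**The case against.** The scoring is explicit, prespecified and attributed to the ARDSnet criteria. Survival is reported separately at 28 and 90 days, so excess deaths would be visible. Patients who deteriorate before dying often spend days ventilated or in organ failure, and those days are deducted. Zero for death is a different composite.

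Part of this stands: credit is not always near full, and mortality is not hidden. But a separate survival result does not repair a score in which a death can beat a survivor, and the deductions do not exclude that.

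A reader might infer three stronger claims, none of which the document supports.
- **That linear regression is laid down for these scores.** The Statistical analysis plan section says only "Continuous data will be analysed using linear regression models, with treatment group as an independent variable along with other important predictors". It names neither VFDs, organ failure free days nor length of stay, and it has a separate rule for time-to-event data. Assigning outcomes to models can be left to the full plan.
- **That power is lost.** Without the missing inputs this cannot be derived. Simulated results go either way, and a rank or ordinal method is weaker for a mortality-only effect.
- **That length of stay has the same flaw.** The article lists it as resource utilisation with costs compared. A short stay before death is a legitimate quantity for that purpose.

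**Conclusion.** The point holds as a defect of ordering in two secondary outcomes. Under the stated rule, a patient unassisted from day 1 who dies on day 14 or day 25 scores 13 or 24, above the article's own survivor at 12. This follows from the definition by arithmetic. The only added premise is an early start of unassisted breathing, which the article expects whenever possible. For organ failure free days it rests on the stated analogy.

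How often inversions would occur, and how far they would move an arm mean, cannot be derived from the document. The primary outcome, the sample size and the survival outcomes are unaffected. This is a worthwhile, cheap improvement and does not threaten the trial's main conclusion.

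**What to change.** In Secondary outcomes, state that any patient who dies on or before day 28 is assigned 0 ventilator free days and 0 organ failure free days, writing the rule out for both. Remove the example of the death on day 25 scoring 9, or replace it with the same patient scoring 0. Report the current scoring as a sensitivity analysis. Settle this before unblinding.

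The cost is wording only. There are two downsides: less direct comparability with studies that credit days before death, which the sensitivity analysis covers, and possibly lower power for an effect on ventilation alone. No change to the regression model or to length of stay is needed for this point.

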#### Translational sub-study

A translational sub-study will run in a subset of patients enrolled in the main trial. In addition to the outcomes above extravascular lung water (PiCCO, Pulsion Medical) will be measured and bronchoalveoalar lavage fluid[25,26] and plasma will be collected to measure markers of inflammation, tissue damage / repair.

### Eligibility criteria

Patients will be eligible for the trial if they fulfil the following criteria:

1. Provision of informed consent

2. Age >18 years

3. Planned elective transthoracic oesophagectomy

4. Ability to use inhaler with spacer device

Patients fulfilling any of the criteria below will be excluded from the trial:

1. Pregnancy

2. Current treatment with long acting beta agonist (any formulation)

3. Allergy to excipients contained in the salmeterol inhaler (HFA 134a)

4. Current treatment with non-cardioselective beta blockers (the cardioselective beta blockers atenolol, betazolol, bisoprolol and metoprolol are permitted).

5. Treatment with an investigational medicinal product in the last 30 days.

### Power and sample size estimate

A systematic review of the literature noted significant variability in the incidence of acute lung injury after oesophagectomy with reports ranging from 14.5 - 43%[5]. Major studies relevant to the UK population include the national CEPOD report which quotes an incidence of 27%[8] and national gastro-oesophageal audit(ASCOTT) which had an incidence 40.5%[7]. An analysis of 6971 patients from Intensive Care National Audit and Research Centre (ICNARC) found that 3352 (47%) fulfilled the oxygenation criteria for ALI in the first 24 hours post operatively[6]. A 5 year audit of oesophagectomies at Heart of England NHS Trust identified that 28% of patients fulfilled criteria for ALI. Based on these data a conservative estimate of the incidence ALI of 25% was selected.

There are no prospective randomised controlled trials in oesophagectomy patients to predict the size of the treatment effect of salmeterol for preventing ALI. In the randomised controlled high altitude pulmonary oedema study, the prophylactic use of salmeterol reduced the incidence of pulmonary oedema from 74 to 33% (55% relative reduction)[13]. LPS challenge studies in humans have shown that salmeterol can reduce neutrophil influx, inflammatory cytokine production and aberrant coagulation by 40-66% relative reduction[12,27]. The study originally set out to demonstrate a 15% absolute reduction in development of acute lung injury. However the study funders requested in 2009 that the study was re-powered to detect a more modest treatment effect. The size of the treatment effect was decided following discussions with the British Society of Oesophageal Gastric Surgeons. Assuming a baseline incidence of lung injury of 25%, consensus was reached that a treatment effect of at least 12.5% (50% relative reduction) was necessary to convince clinicians to translate the treatment into clinical practise should the trial demonstrate that salmeterol prevents ALI/ARDS. This equates to a number need to treat of eight to prevent one episode of lung injury.

To demonstrate this effect with 80% power at a significance level of 0.05 will require 336 patients. To ensure the study maintains sufficient power after drop-outs we have included a 5% failure to proceed to oesphagectomy / receive one lung ventilation and a 2.4% loss to follow-up rate[28]. This gives an overall sample size of 180 per arm (figure 1). This sample size will have 80% power to detect the following relative risk changes in secondary outcomes at a significance level of 0.05: PaO_2 _: FiO_2 _ratio (10%); critical care (35%) and hospital (15%) length of stay; HRQL (15%) and breathlessness(20%).

